## 6.10 Data Collection, Management and Analysis

Data collection, data entry and queries raised by a member of the CHIPPS study team will be conducted in line with the study-specific Data Management Plan, which is held in the e-TMF.

### 6.10.1 Data Collection Methods

Coded data will be collected, by the local researcher, from the recruitment triad's GP practice and care home record systems, paper and/or digital, as appropriate. Collection of data will be on either paper Case Record Forms (CRFs) or electronically onto tablets.

Identification logs, screening logs and enrolment logs will be kept at each of the four University locations in a locked cabinet within a secured room.

Local research staff will receive study protocol training. All data will be handled in accordance with the Data Protection Act 1998.

### 6.10.2 Data Management

Data will be entered into the approved centrally held NCTU CHIPPS database by a member of the CHIPPS study team, in each location and protected using established NCTU procedures.

Any data collected with mobile devices may, according to connectivity and interface, either be entered directly to the database or recorded on the tablet in offline mode with synchronisation with the database, in a consistent manner, at a later time.

Coded data: All participants (GPs, care homes and residents) will be given a unique study Participant Identification Number (PIN). Data will be entered under this identification number onto the centrally held database stored on the servers based at NCTU. Access to the database will be controlled with unique usernames and encrypted passwords, and restricted to members of the CHIPPS study team, and external regulators if requested. The servers are protected by firewalls and are patched and maintained according to best practice. The physical location of the servers is protected by CCTV and security door access.

The database and associated code lists have been developed by the Study Coordinators in conjunction with NCTU. The database software (REDCap) provides a number of features to help maintain data quality, including: maintaining an audit trail, allowing custom validations on all data,

allowing users to raise data query requests, and search facilities to identify validation failure/missing data.

After completion of the study the database will be retained on the servers of NCTU for on-going analysis, for 10 years.

The screening and enrolment logs will remain at the care home, or GP practice. For recruitment monitoring purposes, identifiable patient information will be redacted, and pseudoanonymised copies of these logs, then taken to the research office.

Following consent, identifiable (consented participants only) screening data, linking to the Participant Identification Number, will be held locally at the University research office, in a locked filing cabinet. After completion of the study the identification, screening and enrolment logs will be securely archived at each University research office for 10 years unless otherwise advised by NCTU.

#### **6.10.3 Non-Adherence and Non-Retention**

Adherence to the service specification by the PIP will be measured in several ways – the PIPs will undertake a CHIPPS training programme which will equip them to deliver the intervention. They will be working closely with the care home staff and the resident's GP, and will report regularly to these parties. The study Senior Programme co-ordinators (see 1.4.4.) will also maintain regular contact with the study PIPs to ensure that study procedures are being properly carried out, according to the study training package.. There will also be a random check of the pharmaceutical care plans and associated resident documents by the study geriatricians, to ensure clinical appropriateness and safety, and a formal process evaluation.

Non-retention of the GPs and/or care homes (due to withdrawal of consent) or care home residents (due to consent withdrawal, death or transfer of care) will be recorded (see also section 6.1.3).

#### **6.10.4 Statistical Methods**

##### **6.10.4.1 Statistical Analysis Plan**

The primary outcome ('falls per patient') will mostly likely follow a Poisson distribution and a between group comparison to estimate the difference in falls will be made using a Poisson Regression model. This model will include baseline fall rate, prognostic variables (specified prior to analysis) and group as a fixed factor. The unit of analysis will be the individual participant but, due to the study design incorporating 'clustering' these unit outcomes are likely to be correlated. Therefore, a Generalised Estimation Equation (GEE) approach will be used. The Poisson assumption will be assessed with 'fit' statistics and, if appropriate, a Zero Inflated Poisson, or a Poisson model with an over-dispersion term will be considered.

An analogue GEE model will be used for secondary outcomes, with an appropriate change to the error distribution (e.g. Normal).

The estimate of the between group difference will be provided with a 95% confidence interval and tested at the 5% significance level.

A full Statistical Analysis Plan (SAP) will be written prior to the end of data collection and approved by the study DMC.

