#### Primary Outcome

- fall rate per person at 6 months; as documented in care home falls record

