### 6.6.3 Loss to Follow-up

As the care home residents will be living in the participating care home, loss to follow-up is unlikely. If residents are transferred out of the care home then participation will end at date of transfer. Death is not considered as loss to follow-up in this study.

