## 6.8 Sample Size

A sample size of 880 (440 in each arm) would detect a decrease in fall rate from 1.50 per individual over 6 months to 1.178 with 80% Statistical Power. This assumes that the number of clusters available will be 44, with a mean of 20 participants from each, a loss rate of no more than 20% and an ICC of 0.05 or less.

To balance any under recruitment with over recruitment (eventually balancing out over the whole study), we will recruit in all triads a mean of 20 participants. Any variation with these limits would need to be approved by TSG and or DMC.

These assumptions are based upon data from the CAREMED (29) study, which estimated a fall rate of 1.5 per individual over a 6 months period. The detectable difference (from 1.5 to 1.178) is a relative reduction of 21% which is half that detected within a UK based pharmacist led medication review service provided to care homes.

Data from the CAREMED (29) trial indicated a mortality rate of 33% and further loss to follow-up of 5% over 12 months. Thus, a reasonable estimate of total losses due to mortality or other reasons over 6-months would be 20%. However, we will use data, where possible, up to the point at which someone withdraws from the study (either voluntarily, or otherwise). Therefore, those lost to follow-up, for whatever reason, should contribute some information on falls rate to the study analysis.

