#### **6.10.5 Analysis Population and Missing Data**

The primary analysis will be on the 'Intention-to-Treat' population, i.e. all those randomised and analysed according to the arm to which they were randomised.

It is likely that the proportion of missing data will be small. However, if the proportion of individuals with missing falls data is more than 5% a multiple imputation method (using baseline characteristics) will be used as the basis of a secondary sensitivity analysis.

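### The primary Poisson model lists no time at risk, although the outcome is defined as a fall rate and about one resident in five is expected to die or leave before 6 months

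*Protocol*

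**What the plan says.** **Outcome.** Protocol section 6.5 defines the primary outcome as "fall rate per person at 6 months; as documented in care home falls record". Section 1.3 also calls it a rate.

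**Model.** Section 6.10.4.1 begins from a count: "The primary outcome ('falls per patient') will mostly likely follow a Poisson distribution". It then gives the terms: "This model will include baseline fall rate, prognostic variables (specified prior to analysis) and group as a fixed factor". For clustering it adds: "Therefore, a Generalised Estimation Equation (GEE) approach will be used". Neither this section nor any other part of the protocol mentions an offset, exposure or person-time.

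**Early exits.** Section 6.8 says that "a reasonable estimate of total losses due to mortality or other reasons over 6-months would be 20" per cent, and that data up to the point of leaving will be used where possible, so that leavers add information on the fall rate. Sections 6.6.2 and 6.6.3 end participation at transfer. Section 6.9.2 collects data up to the end of participation. On death, section 6.6.3 states: "Death is not considered as loss to follow-up in this study".

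**Missing data.** Section 6.10.5 expects little missing data and sets one rule: "if the proportion of individuals with missing falls data is more than 5% a multiple imputation method (using baseline characteristics) will be used". The rule serves a secondary sensitivity analysis only.

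**The concern.** Sections 6.5 and 6.8 promise a rate that draws on partial follow-up. The model in section 6.10.4.1, taken as listed, does not estimate one. A Poisson regression of a raw count without time at risk estimates the mean number of falls recorded while each resident was under observation. A resident who dies in week 2 without falling is then coded like a resident who went 6 months without falling. Such short-exposure zeros could also look like excess zeros and push the analysis towards the zero-inflated model that the section allows.

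If the arms differ in how much time residents spend under observation, that difference enters the falls comparison. An arm that loses residents sooner appears to have fewer falls, and an arm that keeps them longer appears to have more. Mortality is a secondary outcome in section 6.5, so the protocol itself allows for an effect on survival.

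The imputation rule has a related gap. It names baseline characteristics as its basis, although falls are also collected at 3 months (section 6.5). It also does not say whether a resident who died counts as having missing falls data.

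**Working it through.** **1. The plan's own sample size.** Inputs from section 6.8: "A sample size of 880 (440 in each arm) would detect a decrease in fall rate from 1.50 per individual over 6 months to 1.178", 80% power, 44 clusters averaging 20 residents, loss up to 20%, ICC up to 0.05. Two-sided 5% is assumed from the 95% interval in section 6.10.4.1.

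- Individually randomised, per arm: (1.960 + 0.842)² × (1.5 + 1.178) / 0.322² = 202.7
- Design effect on the retained cluster size of 16: 1 + 15 × 0.05 = 1.75, giving 354.8
- Allowing for 20% loss: 354.8 / 0.80 = 443.5 per arm, 887 in total

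This is within 0.8% of 880, so the stated size reproduces.

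**2. The expected loss.** Section 6.8 cites 33% deaths plus 5% other loss over 12 months. Half of 38% is 19%; at constant hazard, 1 − √0.62 = 21.3%. The 20% is consistent with its source. On 880 residents it means 0.20 × 880 = 176 with shortened follow-up.

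**3. Effect of leaving out time at risk.** Let d be the share of an arm that leaves and f the mean fraction of the 6 months for which leavers are observed. Mean exposure is 1 − d(1 − f). Without an offset, the estimated ratio equals the true ratio multiplied by (intervention exposure / control exposure). The protocol does not give f or the loss by arm. Both are assumptions here, with f = 0.5 as the central case and 0.25 to 0.75 as the range.

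| Loss, control vs intervention | Exposure, control vs intervention (f = 0.5) | Ratio shown when truth is 1.00 | Range, f = 0.25 to 0.75 |
|---|---|---|---|
| 20% vs 20% | 0.900 vs 0.900 | 1.000 | 1.000 |
| 18% vs 22% | 0.910 vs 0.890 | 0.978 | 0.965 to 0.990 |
| 15% vs 25% | 0.925 vs 0.875 | 0.946 | 0.916 to 0.974 |
| 25% vs 15% | 0.875 vs 0.925 | 1.057 | 1.027 to 1.092 |

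Constant-hazard leaving gives mean exposure of 0.923 at 15% loss and 0.869 at 25%, and 0.869 / 0.923 = 0.94, in agreement with the third row. If the true ratio is the design value of 0.785, it appears as 0.743 under 15% vs 25% and as 0.830 under 25% vs 15%.

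**4. Simulation.** An exchangeable Poisson GEE was fitted to 22 clusters of 20 per arm in 400 runs per scenario. Cluster multipliers were gamma with variance 0.05, and leavers exited at a uniformly distributed time.

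| Loss, control vs intervention | True ratio | Estimate without offset | Estimate with offset | Rejections without offset | Rejections with offset |
|---|---|---|---|---|---|
| 20% vs 20% | 1.00 | 0.996 | 0.996 | 8.0% | 8.3% |
| 15% vs 25% | 1.00 | 0.956 | 1.010 | 10.3% | 7.5% |
| 25% vs 15% | 1.00 | 1.059 | 1.003 | 11.8% | 7.3% |
| 20% vs 20% | 0.785 | 0.782 | 0.784 | 78% | 80% |
| 15% vs 25% | 0.785 | 0.736 | 0.777 | 91% | 79% |
| 25% vs 15% | 0.785 | 0.834 | 0.789 | 51% | 75% |

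Monte Carlo error on the power figures is about 2 percentage points. Rejection stays above 5% under the null even with the offset because the robust standard errors were left uncorrected with 44 clusters. That is a separate matter; the comparison to read here is with versus without the offset.

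**5. Sample size after the fix.** With 440 per arm contributing 90% of person-time and a design effect of 1 + 19 × 0.05 = 1.95, the standardised difference is 0.322 × 0.9 / √(2.678 × 0.9 / (440 / 1.95)) = 2.80, giving 80.1% power. The total of 880 stands.

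**The case against.** **The list may be only an outline.** Section 6.10.4.1 defers to a full statistical analysis plan, which is not at hand, and even leaves the prognostic variables open. Nothing in it rules out an offset, and sections 1.3, 6.5 and 6.8 show that a rate using partial follow-up is intended. This stands as far as intent goes: the analysis plan could supply the term. It does not remove the mismatch, because the protocol does name the modelled quantity and the model terms, and these do not deliver the rate defined elsewhere.

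**There is no bias under equal loss.** This is correct. The 10-point differences used above have no basis in the documents, and the direction of any bias is unknown.

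**Imputing falls after death.** A reader might infer that the 5% rule would create falls for residents who have died. No section says so. Section 6.6.3 does not treat death as loss to follow-up, sections 6.8 and 6.9.2 point towards using data up to exit, and the imputation is a secondary sensitivity analysis that leaves the primary estimate untouched. What stands is narrower: the protocol leaves open whether deaths count under the rule.

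**Small missingness against 20% losses.** A reader might also see a contradiction between sections 6.10.5 and 6.8. It is not established. If early leavers have observed falls up to exit, losses can be 20% while missing falls data are few.

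**Conclusion.** The point holds for the primary model. As listed, it compares falls recorded while observed, whereas the outcome is a rate, and its rate ratio is unbiased only when mean exposure is the same in both arms. A 10-point difference in loss shifts the ratio by about 5% to 6% in the central case (roughly 3% to 9% across the timing assumptions), in either direction. In the 15% versus 25% case that is (1 − 0.946) / (1 − 0.785), about a quarter of the target reduction. A 4-point difference shifts it by about 2%, and equal loss by nothing. These sizes rest on assumed loss by arm and assumed timing of exit, neither of which the protocol gives.

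On imputation, the supportable point is that the status of deaths under the 5% rule is undefined and that the stated basis leaves out observed 3-month falls. The documents do not support a claim that falls after death will be imputed, or that the primary result is certain to be biased. This is a free improvement to stated methods.

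**What to change.** **Primary analysis (section 6.10.4.1).**
- Define the outcome as the number of falls from time zero to the earliest of 6 months, death, transfer or withdrawal.
- Add log(time at risk) as an offset in the Poisson GEE, and in any over-dispersed or zero-inflated alternative.
- Report deaths and transfers by arm beside the result. The offset yields a rate while residents are alive and in the home; it does not remove bias if those who leave differ in fall risk.

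**Sensitivity analysis (section 6.10.5).**
- State that follow-up ended by death is not missing falls data, consistent with section 6.6.3.
- Limit imputation to living residents whose falls record is missing.
- Include arm, cluster and observed 3-month falls in the imputation model, as well as baseline characteristics.

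**Cost.** Analysis wording, with no change to the 880. Section 6.10.3 already records non-retention through death, transfer or withdrawal, and section 6.6.3 refers to the date of transfer. The protocol does not say that every exit date is recorded, so the date should be captured with the reason.

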#### 6.11.1.2 Interim Analyses

No efficacy interim analyses are planned. Analysis of recruitment rates, withdrawal rates etc. will be monitored as part of the internal pilot and full trial.

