#### 6.11.2.1.3 Notification of SUSARs and Safety Concerns to the DMC

The independent DMC will review the frequency of SAEs (deaths and hospitalisations) and falls. The form and frequency of DMC review of safety data will be documented in the Safety Management Plan and the DMC Terms of Reference (both documents are held in the e-TMF). In addition, further monitoring and substantiation of the process will be undertaken at the recommendation of the DMC.

The DMC will review unblinded data to evaluate safety measures at GP practice level (i.e. across all care homes associated with the GP practice) and at care home level (i.e. within each individual care home). The DMC will review safety data on a regular basis and recommend actions to the PSC and via the PSC to the Trial Management Group. If safety is identified as an issue by any of the trial oversight groups a substantial amendment to the protocol would be submitted to REC.

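### Fit statistics may bring in a zero-inflated Poisson that does not estimate the fall rate ratio, and the body that approves the SAP can in effect see falls by arm

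*Protocol*

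**What the plan says.** **Outcome and model.** The primary outcome in section 6.5 is "fall rate per person at 6 months; as documented in care home falls record". Section 6.10.4.1 says that "a between group comparison to estimate the difference in falls will be made using a Poisson Regression model". Because residents are clustered, it adds: "Therefore, a Generalised Estimation Equation (GEE) approach will be used". The Poisson assumption is then to be checked with fit statistics that are not named and, "if appropriate, a Zero Inflated Poisson, or a Poisson model with an over-dispersion term will be considered". The section gives no threshold, no order of preference between the two alternatives, and no statement of which part of a ZIP would carry the test. It promises one between-group estimate with a 95% confidence interval and a test at 5%.

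**Approval of the SAP.** The same section states: "A full Statistical Analysis Plan (SAP) will be written prior to the end of data collection and approved by the study DMC". Section 6.11.2.1.3 gives that committee's safety remit: "The independent DMC will review the frequency of SAEs (deaths and hospitalisations) and falls". It continues: "The DMC will review unblinded data to evaluate safety measures". These reviews are at GP practice and care home level and take place regularly. Section 6.11.1.2 says "No efficacy interim analyses are planned".

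**The concern.** There are two separate points.

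1. **The estimand could change with the model.** The trial is sized on a marginal fall rate per resident. A ZIP replaces that single contrast with an odds ratio for being an excess zero and a rate ratio among everyone else. If it became the reported primary analysis, a real reduction in falls could show as little or no effect in the count part, simply because it came about through more residents not falling at all. A ZIP is also not a standard GEE, so the clustering method named in the same paragraph does not carry over without further choices.

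2. **The approver of the SAP may know the direction of the primary outcome.** The SAP is the natural place to settle the model. It can be approved at any time up to the end of data collection, by a committee whose safety remit covers falls and unblinded data. Even if the committee acts properly, the record could not show that the analysis was fixed without knowledge of falls by arm.

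**Working it through.** **Step 1. What the trial is sized on (section 6.8).** Inputs: 1.50 versus 1.178 falls per person over 6 months, 80% power, 5% level (taken as two-sided), mean 20 per cluster, 20% loss, ICC 0.05.

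- Per arm before clustering: (1.960 + 0.842)² × (1.50 + 1.178) / (1.50 − 1.178)² = 202.7.
- Design effect with 16 left per cluster: 1 + (16 − 1) × 0.05 = 1.75.
- Per arm: 202.7 × 1.75 / 0.8 = 443.5, so 887 in total against the stated 880.

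The stated figure is reproduced to within 1%. The target is therefore the marginal rate ratio 1.178/1.50 = 0.785.

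**Step 2. What a ZIP estimates.** The marginal mean is the share of residents who are not excess zeros (here called susceptible) times their mean count. So the marginal ratio equals the susceptible-share ratio times the count-part ratio. The two ratios of interest agree only if treatment leaves the susceptible share unchanged.

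Assume for illustration that 60% of control residents are susceptible, with 2.5 falls each: 0.60 × 2.5 = 1.50. The 60% and 2.5 are not from the protocol. Three routes lead to the same 1.178:

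| How the effect arises | Intervention share × count mean | Marginal ratio | Count-part ratio |
|---|---|---|---|
| Fewer susceptible residents only | 0.471 × 2.5 | 0.785 | 1.00 |
| Mixed | 0.50 × 2.356 | 0.785 | 0.94 |
| Fewer falls per susceptible resident only | 0.60 × 1.963 | 0.785 | 0.785 |

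**Step 3. Simulation of the first row.** 44 clusters of 16, cluster SD 0.3 on the log scale, 300 replicates. The Poisson GEE (exchangeable, bias-reduced robust errors) estimated 0.784. The ZIP count part estimated 0.996 and was significant in 8% of runs with cluster-robust errors, within the 5–8% that the same test gave with no effect at all.

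**Step 4. Could fit statistics prompt the switch?** AIC preferred ZIP to a plain Poisson in every run of the five scenarios completed. Two of these used negative-binomial data with no zero inflation.

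**Step 5. Is the switch needed?** A Poisson GEE needs a correctly specified mean, not Poisson variance. With no effect, it rejected in 4–6% of runs across the over-dispersed and zero-inflated scenarios (Monte Carlo error about ±2.5 points). A ZIP with model-based errors that ignored clusters rejected in 24–37%, so moving to a ZIP also means rebuilding the clustering adjustment.

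**Step 6. What the DMC can see.** Set side by side: section 6.11.2.1.3 has the DMC reviewing falls, and in its next paragraph unblinded safety data at practice level. Sections 5.1.1 and 6.7 make the practice (triad) the randomised unit. Section 6.11.2 adds safety data for each arm. Unblinded falls by practice can be added up to falls by arm. Section 6.10.4.1 gives no deadline for the SAP other than the end of data collection.

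**The case against.** Most of the other side's case is fair.

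- **The Poisson GEE is the named default.** Alternatives are only to be considered, and the over-dispersed Poisson keeps the same rate ratio. This stands, so the estimand problem belongs to ZIP alone.
- **The SAP may settle the matter.** The SAP is not to hand and may make ZIP a sensitivity analysis. This stands as far as thresholds and details go. It does not remove the fact that the protocol itself admits a model with a different effect measure, and it does not touch who approves the SAP.
- **Nothing says the fit check uses allocation.** Correct. A reader might infer that the model will be picked on unblinded data, but the text does not say so, and a pooled, blinded check is possible.
- **Falls by arm is an inference.** No single sentence states it. Section 6.11.2 lists admissions and deaths when it describes data for both arms, and the form and frequency of review are left to the Safety Management Plan and the DMC Terms of Reference. The inference is strong because practices are randomised, but it remains an inference.
- **The 1.00 is an extreme.** It puts the whole effect on non-falling and reads only the count part. If the effect is on falls per susceptible resident, the two ratios agree at 0.785.
- **Type I error.** A reader might infer that the 5% level is shown to be inflated. It is not. Rejecting whenever either the GEE or the robust ZIP was significant gave 8–11%, but that is selection by p-value. Selection by fit was not simulated.

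Section 6.11.1.2 is not contradicted either: a safety review of falls is not an efficacy interim analysis.

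**Conclusion.** The point holds in two limited parts.

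First, section 6.10.4.1 allows a ZIP to be considered for the primary outcome on the basis of fit, although a ZIP has no single group effect equal to the fall rate ratio. For a true marginal ratio of 0.785, the count-part ratio lies between 0.94 and 1.00 in the two illustrative cases where the intervention makes some residents non-fallers. It equals 0.785 only where the susceptible share does not change. These values rest on the assumed 60% susceptible and 2.5 falls each. The general result, that the ratios differ whenever the susceptible share changes, does not depend on them. The default analysis already copes with the problem that the switch is meant to solve.

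Second, the SAP's approver reviews falls and unblinded practice-level data regularly, and nothing requires approval to come first. This is a risk to demonstrable pre-specification. It is not evidence that the DMC will choose the model, since the protocol has it approve the SAP and does not say that it writes it. Nor is it evidence of bias.

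This should be changed, but it does not invalidate the design.

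**What to change.** 1. In section 6.10.4.1, state that the primary analysis is the rate ratio from the Poisson GEE, with the triad as cluster and cluster-robust standard errors, whatever the fit statistics show. List ZIP and any other count model as sensitivity analyses only. The small-sample correction and degrees of freedom can be left to the SAP.
2. Have the SAP approved by a body without access to falls by arm, for example the Programme Steering Committee with blinded statisticians. Alternatively, keep the DMC as approver but require sign-off before it first receives unblinded falls data. If it has already received them, record the date.

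The cost is a few sentences and a change of approver or timing. No data collection changes, and the sample size is unaffected.
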